## Abstract

**Background::**

Several studies have suggested that intestinal flora may play an important role in allergic diseases. The purpose of this study was to investigate the effect of probiotics of Bifidobacterium triplex on the symptoms of allergic rhinitis (AR). The effects of this probiotic on the immune system have been reported in some studies, but most previous studies have been in animals.

**Methods/Design::**

60 infants and young children with AR were randomly divided into 2 groups: probiotics/placebo group. The main outcome was the use of a comprehensive symptom drug score to assess allergy symptoms. In addition, health-related quality of life was investigated (rhinitis quality of life questionnaire). Secondary outcomes included a visual analog scale of allergy burden and a second quality of life questionnaire. This report describes the study design of a randomized controlled trial.

**Discussion::**

The study design described a double-center, randomized, location at the Minda Hospital of Hubei Minzu University and West China Hospital of Sichuan University, which will be focused on the study about probiotics treatment and its effect on AR symptoms.

**Trial registration::**

It has been registered at http://www.chictr.org.cn/listbycreater.aspx (Identifier: ChiCTR2000031175), Registered March 22, 2020.

## Introduction

1

Allergic rhinitis (AR) is a non-infectious inflammatory disease of nasal mucosa mediated by specific IgE after exposure to allergens in susceptible infants and young children.^[1]^ AR is mainly characterized by clinical manifestations such as clear watery nose and nasal congestion, which can be accompanied by eye symptoms and ear symptoms. AR is life-threatening, however it can significantly affect the quality of life of infants and young children, leading to poor sleep quality and lack of concentration, which seriously affects the growth and development of infants and young children. In addition, AR is also closely related to asthma, nasal polyps, sinusitis, otitis media and other diseases. The prevalence of AR has been increasing year by year globally, ranging from 2.2% to 45.1%.^[2]^ With the rapid development of society and changes in living environment, the incidence of AR among infants and young children in China is also increasing, which seriously affects the physical and mental health of infants and young children.^[3]^

In recent years, Sakaguchi et al found that the TH_1_ / TH_2_ immune response imbalance of CD4 + T lymphocytes plays an important role in the pathogenesis of AR. This theory is to discuss the pathogenesis of AR from the perspective of immunology.^[4]^ The strong TH_2_ cell reaction plays an important role in the occurrence and development of AR.

Probiotics and breast milk are identified as two factors that can affect the course of allergic disease. The effect of probiotics on immune function has been a hot topic in allergic diseases in recent years. It has been reported that probiotics can improve the intestinal mucosal immune function of allergic rats and down-regulate the function of TH_2_ cytokines to mediate the TH_1_/ TH_2_ balance, thus preventing the occurrence of food allergy. Animal experiments have found that lactic acid bacteria can promote TH_1_ immune response and inhibit TH_2_ immune response, so as to put the body's immune system in a dynamic balance and inhibit the occurrence of allergic reactions.^[5]^

Prebiotics are defined by Gibson and Roberfroid, first proposed in 1995: Prebiotics are undigested or indigestible food ingredients that contribute to host health by selectively stimulating bacterial proliferation and/or activity in the colon. Some studies have found that breastfeeding within 6 months after birth is a protective factor for AR in infants and young children, and Odijk et al^[6]^ found that breastfeeding for more than 3 months can effectively reduce the probability of infants suffering from ectopic dermatitis and laryngeal wheezing, especially for those infants and young children with a family history of allergies. One of the reasons that breast-fed infants are less susceptible to allergic diseases than artificially fed infants is the presence of beneficial oligosaccharides in breast milk. Bifidobacteria dominated the intestinal flora of breast-fed infants at 6 to 7 days, while the number of bifidobacteria in the intestinal flora of artificially fed infants was small and the bacterial species was diverse. In present study, we aim to conduct a double-blind randomized controlled trial study to explore the effect of probiotics on AR in infants and young children.

## Methods/design

2

### Research object

2.1

2.1.1 We aim to explore the role of probiotics in preventing allergic diseases in infants and young children.

2.1.2 We aim to explore the effect of probiotics on AR in infants and young children.

### Study method

2.2

A total of 60 patients with AR in Otorhinolaryngology-Head and Neck Surgery, Minda Hospital of Hubei Minzu University and West China Hospital of Sichuan University from May 2020 to April 2022 will be selected and randomly divided into probiotic/placebo group according to the numerical table. The study divided the patients into two groups. Patients will be divided into a double-blind probiotic/placebo study, we will assess allergy Symptoms using health-related quality of life by means of diaries, quality of life problems (RQLQ), and Combined Symptoms and Medication Score (CSMS). CSMS is a simple and standardized way to balance symptoms with the need for antidepressants. RQLQ is a disease-specific indicator used to assess health-related quality of life, including the patient's physical, social and emotional health.

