### Participants

2.3

Inclusion criteria include the following:

(1)We will recruit and include 60 participants aged 0 to 6 with a history of AR.(2)The plan has an equal proportion of male and female, however this is not enforced.(3)AR must be diagnosed by a doctor (allergist or general practitioner).(4)Participants were required to present the results of tests sensitive to air allergen IgE (either skin prick test or serum allergen-specific IgE) no more than 24 months prior to the trial.

Exclusion criteria include the following:

Patients with a history of diabetes, gastrointestinal disease, use of antibiotic drugs in the past 6 weeks, and any known psychiatric or neurological disorders.

Anatomical changes such as septal rupture or perforation were also ruled out.

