### Blinding and random

2.7

After completing the first evaluation (the first interview), the research assistant opened an opaque envelope to determine that the participants were randomly assigned to two groups. Randomization is based on a computer-generated sequence of random Numbers built by an independent investigator. These researchers will be independent of the study members responsible for recruiting participants. All outcome measurements will be performed by blind experimenters.

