### Statistical analysis

2.8

Statistical analyses will be implemented by SPSS 17.0 and Microsoft Excel 2007 software. Data will be represented as mean ± standard deviation (SD). A *t*-test will be performed to compare the changes in measures within groups. Statistical significance will be considered at *P* < .05.

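### The random sequence is described in two ways and no balancing by centre is described; the likely cost is precision, not bias

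*Protocol article*

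**What the plan says.** Section 2.2 (Study method) has patients "randomly divided into probiotic/placebo group according to the numerical table". Section 2.7 (Blinding and random) says "Randomization is based on a computer-generated sequence of random Numbers built by an independent investigator", and keeps those who build the sequence apart from those who recruit. After the first evaluation, "the research assistant opened an opaque envelope to determine that the participants were randomly assigned to two groups".

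The setting is "Minda Hospital of Hubei Minzu University and West China Hospital of Sichuan University from May 2020 to April 2022", and the sample size is given as "We will recruit and include 60 participants aged 0 to 6 with a history of AR". Section 2.8 (Statistical analysis) states: "A *t*-test will be performed to compare the changes in measures within groups". It mentions no centre term.

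The article does not give the allocation ratio, the expected number of children per hospital, or any blocking or stratification. Nor does it say that randomisation is simple or unrestricted.

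**The concern.** Two hospitals working from one text need one account of where the allocation comes from. Section 2.7 carries the safeguards: an independent sequence builder, separation from recruiting staff and an opaque envelope. Section 2.2 names another source and repeats none of them.

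Balance is a separate matter. With 60 children at two sites, a list that ignores centre can leave a visibly different mix of hospitals in the two arms. If outcomes differ between hospitals, that mix adds noise to the treatment difference, and the stated analysis does nothing to remove it. At stake are precision and the look of the baseline table, in a trial with little precision to spare.

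**Working it through.** **1. The two descriptions.** Section 2.2 names a number table with no holder and no concealment. Section 2.7 names a computer-generated sequence, an independent builder and envelopes. They could be the same thing loosely worded, but the text does not say so.

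**2. Inputs.** From the article: 60 children, two arms, two hospitals, significance at P < .05. The 60 cannot be reproduced, because no effect size, SD or power is given, so it is taken as stated. Assumptions: 1:1 allocation, two-sided test, unit SD within centre, m children at the smaller hospital (10 to 30), centre effect D of 0.5 or 1 SD on the analysed measure, and a between-arm t-test.

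**3. Chance of a centre-share gap of at least 20 percentage points, without stratification.**
- Arms fixed at 30:30: k ~ Hypergeometric(60, m, 30), gap = |k − (m − k)|/30.
- Simple randomisation: k ~ Bin(m, 0.5), j ~ Bin(60 − m, 0.5), gap = |k/(k + j) − (m − k)/(60 − k − j)|.

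| Centre split | Simple | Arms fixed 30:30 |
|---|---|---|
| 10:50 | 4.2% | 8.0% |
| 15:45 | 8.7% | 7.2% |
| 20:40 | 12.2% | 17.0% |
| 30:30 | 15.5% | 19.6% |

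**4. Precision.** With balance within centre, the SD of the treatment difference is √(2/30) = 0.258. With arms fixed at 30:30 and no stratification, the variance is 2/30 + D² × 4p(1 − p)/59, where p = m/60. At p = 0.5:
- D = 0.5: 0.0667 + 0.25/59 = 0.0709, a ratio of 1.064.
- D = 1: 0.0667 + 1/59 = 0.0836, a ratio of 1.254.

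A simulation of 20,000 trials per scenario gave SDs of 0.267 and 0.289, so ratios of (0.267/0.258)² ≈ 1.07 and (0.289/0.258)² ≈ 1.25. The same formula at 10:50, where 4p(1 − p) = 0.556, gives increases of 3.5% and 14.1%.

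**5. Bias and type I error.** In the same simulations (arms 30:30; centres 15:45 and 30:30; D = 0, 0.5 and 1), the mean bias was at most 0.003 SD in absolute value. The unadjusted between-arm t-test rejected in 4.8% to 5.1% of null trials.

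**6. Why the centre term is needed as well.** If the list is stratified but the t-test ignores centre, the within-arm variance at D = 1 and centres 30:30 is about 1 + 1/4. The standard error used is then about √(2 × 1.25/30) = 0.289, although the true SD is 0.258. The gain exists but the test does not use it.

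**The case against.** The best reply is that this is a condensed article. Block structure and strata are commonly left to the full protocol, and a computer-generated list may well be blocked and stratified. Section 2.2 is a summary, section 2.7 is the operative text, and a numerical table may simply mean the list of section 2.7. Much of this stands: silence is not a statement that randomisation is unrestricted, and the conflict of wording is modest. It remains that two sources are named without reconciliation, and that the stated analysis has no centre term.

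A second reply is that section 2.8 analyses changes, which removes stable differences in level between hospitals. That also stands. The assumed D must therefore be read as a centre difference in change, which may be small.

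A reader might infer more than the article supports:
- **Confounding of centre with treatment.** Under concealed randomisation any imbalance is by chance, is zero on average and is covered by the type I error (step 5).
- **Seasonal bias over the 24 months of enrolment.** The article gives no figure for seasonal variation and does not restrict the allergens to seasonal ones. Chance imbalance in season would also be unbiased.
- **A predictable table read at the clinic.** Nothing says where the table is kept or who reads it, and section 2.7 describes envelopes.
- **Uneven arms within a hospital as the measure of harm.** With 30 children per hospital, simple randomisation gives 10:20 or worse in at least one hospital in 18.8% of trials. That counts arm sizes: if both hospitals split 10:20 in the same direction, centre share is equal in the two arms. Step 3 uses the relevant quantity.

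**Conclusion.** The point holds in a limited form. Sections 2.2 and 2.7 describe the random sequence inconsistently and should be reconciled. Neither describes balancing by centre, and section 2.8 does not adjust for it. On the stated concealed procedure, the treatment comparison is not biased and type I error is held.

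The possible loss is in face balance and precision, of the size shown in steps 3 and 4. Both figures apply only if the list is in fact unstratified, which the article does not say. They rest on the assumed 1:1 ratio, centre split and centre effect; with no centre effect there is no loss of precision. The inconsistent wording is a plain correction. The balancing and the centre term are a recommended improvement on what is stated.

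**What to change.** - **Section 2.2:** delete the reference to the numerical table, so that section 2.7 is the single description.
- **Section 2.7:** specify computer-generated permuted blocks of randomly varying size, stratified by centre, with the list held by the independent investigator. The article says who builds the list but not who keeps it.
- **Section 2.8:** include centre as a factor in the between-arm analysis.

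If the full protocol already specifies a blocked list stratified by centre, the article needs only matching wording and the centre term.

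The cost before enrolment is a few lines of text and a list generated in this way. The one downside is slightly more predictability within a block, which varying block sizes limit.

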### Participants

2.3

Inclusion criteria include the following:

(1)We will recruit and include 60 participants aged 0 to 6 with a history of AR.(2)The plan has an equal proportion of male and female, however this is not enforced.(3)AR must be diagnosed by a doctor (allergist or general practitioner).(4)Participants were required to present the results of tests sensitive to air allergen IgE (either skin prick test or serum allergen-specific IgE) no more than 24 months prior to the trial.

Exclusion criteria include the following:

Patients with a history of diabetes, gastrointestinal disease, use of antibiotic drugs in the past 6 weeks, and any known psychiatric or neurological disorders.

Anatomical changes such as septal rupture or perforation were also ruled out.

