### Measurement of outcomes

2.6

Tools to measure primary indicators include the following:

(1)The health-related quality of life by means of diaries.(2)In this study, RQLQ will be used to evaluate the comfort level of the 2 groups of patients.(3)CSMS will be used to evaluate allergy symptoms.

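### The eligibility criteria do not require current symptoms or current need for medication, although the main outcome is a symptom and medication score and the population is elsewhere described as children with AR

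*Protocol article*

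**What the plan says.** The protocol article describes its population in two ways.

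- **Children who have AR.** The abstract (Methods/Design) says "60 infants and young children with AR were randomly divided into 2 groups: probiotics/placebo group". Section 2.2 says "A total of 60 patients with AR in Otorhinolaryngology-Head and Neck Surgery", at two hospitals, selected between May 2020 and April 2022.
- **Children who have had AR.** Section 2.3, the list that decides entry, says "We will recruit and include 60 participants aged 0 to 6 with a history of AR". It adds a diagnosis by an allergist or general practitioner, with no date and no statement about disease activity. It also asks for a skin prick or serum IgE result "no more than 24 months prior to the trial".

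The exclusions in section 2.3 concern diabetes, gastrointestinal disease, recent antibiotics, psychiatric or neurological disorders and nasal anatomy. None concerns disease activity. No section sets a minimum symptom or medication score, a symptomatic period or a season.

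On the outcome, the abstract says "The main outcome was the use of a comprehensive symptom drug score to assess allergy symptoms", and section 2.6 says "CSMS will be used to evaluate allergy symptoms". Section 2.7 places a first evaluation before the envelope is opened. Section 2.8 describes the t-test as a comparison of changes within groups.

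**The concern.** A trial that measures symptoms and medication use needs children in whom these can differ between probiotic and placebo. A child whose rhinitis has settled, and who stays free of symptoms and medication throughout, scores zero in either arm. That child counts among the 60 but carries no information on the treatment.

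If there are several such children, a probiotic that helps symptomatic children shows a smaller average effect, and a null result becomes hard to read. It could mean that the product does not work, or that too few children had anything to treat. The two descriptions of the population also leave open which children the result would apply to.

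**Working it through.** **Step 1: does any stated criterion exclude a symptom-free child?** Take a child aged 5 with a past diagnosis of AR, an IgE result 18 months old, no current symptoms, no medication and none of the listed exclusions.

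- Age and history: met.
- Doctor's diagnosis: met, since no date or activity is asked for.
- IgE result within 24 months: met. In any case this documents sensitisation, not symptoms.
- First evaluation (section 2.7): it precedes allocation, but no threshold is attached to it.

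The child is eligible under section 2.3. Whether the child is one of the patients with AR in section 2.2 depends on how that phrase is read.

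**Step 2: inputs for the size.** From the documents: 60 children, two groups, significance at 0.05. Not in the documents: the allocation ratio (30 per arm assumed), sidedness (two-sided assumed), effect size, SD, and the share f of children free of symptoms and medication throughout. The article gives no sample-size calculation, so there is no stated figure to reproduce.

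**Step 3: mean difference.** Let δ be the mean difference in children who have symptoms or need medication. The remaining share f contributes zero, so the overall difference is (1 − f)δ.

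- f = 20%: 80% of δ remains.
- f = 30%: 70% of δ remains.

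**Step 4: information if the SD is unchanged.** Information scales with the square of the effect, so the equivalent number of symptomatic children is 60(1 − f)².

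- f = 20%: 60 × 0.64 = 38.4.
- f = 30%: 60 × 0.49 = 29.4.

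As an illustration, 30 per arm has 80% power for a standardised difference of 0.72 (normal approximation). With that difference in symptomatic children, power falls to 61% at f = 20% and to 50% at f = 30%.

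**Step 5: information if the SD changes.** Let symptom-free children score zero and the others have mean m and SD s. The variance of the mixture is (1 − f)(s² + f·m²). With r = m/s, the share of information kept is

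(1 − f)² / [(1 − f)(1 + f·r²)] = (1 − f) / (1 + f·r²).

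| f | r = 0 | r = 1 | r = 2 | SD unchanged |
|---|---|---|---|---|
| 20% | 60 × 0.8 = 48 | 60 × 0.8/1.2 = 40 | 60 × 0.8/1.8 ≈ 27 | 38 |
| 30% | 60 × 0.7 = 42 | 60 × 0.7/1.3 ≈ 32 | 60 × 0.7/2.2 ≈ 19 | 29 |

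The unchanged-SD figure lies inside the range. The true loss could be smaller or larger. Even in the mildest case (r = 0) the symptom-free children's share of the information is lost.

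**The case against.** **The natural reading is clinic patients with AR.** The abstract, section 2.2 and the diagnosis criterion together suggest children attending ear, nose and throat departments because they have the disease. This stands in part. It probably keeps f low, but it is not an eligibility rule, and the looser wording sits in the list that governs entry.

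**The article is condensed.** A baseline threshold might stand in a fuller protocol. That is possible. But the article does not leave eligibility to another document. It states criteria, and those criteria do not match its own description of the population or its outcome.

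**Prevention is also an aim (section 2.1.1).** It is, but the main outcome and the stated focus concern AR symptoms, in children who already carry the diagnosis.

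**Stronger readings that the documents do not support.**

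- *Every child at zero on entry is wasted.* A child enrolled before a pollen season can show a smaller rise on probiotic than on placebo, and that is a valid contrast. A child controlled by medication is not at zero on a score that counts medication. Only children free of both throughout add nothing.
- *The 24-month window for the IgE test is itself the fault.* The test shows sensitisation, and a fresher one would not establish current symptoms.
- *The result would be biased.* Randomisation still protects the comparison. What suffers is sensitivity and interpretation.
- *A specific number of children is lost.* The documents give no value for f, the effect or the SD.

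**Conclusion.** The concern holds in a limited form. Section 2.3 admits children without current symptoms or medication need, whereas the abstract and section 2.2 speak of children with AR and the main outcome measures symptoms and medication. Children who remain free of both dilute the effect in proportion to their share: 80% of the mean difference is kept at f = 20%, and 70% at f = 30%.

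These values of f are assumptions, and the proportion rests on such children contributing exactly zero difference. The equivalent sample sizes also depend on the SD: about 27 to 48 children at f = 20%, and 19 to 42 at f = 30%, for r between 0 and 2. Recruitment from specialist departments may keep f below this range. The point is worth correcting because a trial of 60 has little information to spare and the correction is cheap. It does not invalidate the comparison.

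**What to change.** Use one population definition in the abstract, section 2.2 and section 2.3: doctor-diagnosed AR with current symptoms or current need for AR medication. Confirm it by a CSMS above zero at the first evaluation, before the envelope is opened. Keep the IgE criterion as evidence of sensitisation.

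Selecting on a baseline score invites regression to the mean, so scores would tend to fall in both arms without any treatment effect. The effect should therefore be judged by the comparison between groups, and the within-group wording in section 2.8 should be changed to say so.

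The cost is an amendment of wording, some screen failures and slower recruitment out of season, within a two-year window for 60 children. The first evaluation already precedes allocation, so a new visit should not be needed if CSMS is scored there. If it is scored from diaries, which the article does not make clear, a short recording period before allocation would be required. Screening at entry lowers f but does not make it zero, because symptoms may settle during the trial phase.
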